#### 7.1.1 PREGNANCY

Any pregnancy that occurs during study participation must be reported to the Investigator/sponsor. To ensure subject safety, each pregnancy must be reported to the Sponsor immediately. The pregnancy must be followed up to determine outcome (including premature termination) and status of mother and child. Pregnancy complications and elective terminations for medical reasons must be reported as an AE or SAE. Spontaneous abortions must be reported as an SAE.

Any SAE occurring in association with a pregnancy brought to the Investigator's attention after the subject has completed the study and considered by the Investigator as possibly related to the investigational product, must be promptly reported to the Investigator/sponsor.

In addition, the Investigator must attempt to collect pregnancy information on any female partners of male study subjects who become pregnant while the subject is enrolled in the study. Pregnancy information must be reported to the Investigator/sponsor as described above.

## 7.2 DOCUMENTATION OF (S)AES

All adverse events, including intercurrent diseases, must be documented in the subject record and subsequently in the eCRF.

When an adverse event occurs, regardless of the causal relationship between the event and the IMP, the affected subject must always be monitored until symptoms subside or pathological laboratory values return to baseline, or until no further findings are expected in the opinion of the principal coordinating investigator (PCI). If the adverse event develops into a persistent secondary disease, it should be classified as an SAE and documented accordingly at the end of the trial. All findings and results must be documented both in the subject's record and on the corresponding adverse event form in the eCRF.

The following information is required:

- type of adverse event (sign, symptom or disease, if possible medical term),
- assessment of the (worsening of existing) concomitant diseases as an adverse event,
- classification (serious/ non-serious),
- start and end of occurrence,
- CTCAE Grade (Version 5.0, published 27.11.2017, NCI)
- causality to the IMP (not -, unlikely -, possibly -, probably -, certainly related, unknown or not assessable)
- action taken regarding the IMP (dose not changed, dose reduced, dose increased, temporarily interrupted, drug withdrawn, unknown, not applicable),
- action taken in order to restore or improve the well-being of the subject (none, drug treatment, other)
- outcome of the event (recovered, recovering, not recovered, recovered with sequelae, fatal, unknown).

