### 3.3 SECONDARY END POINTS

- Single components of the primary outcome
- Episodes of infection and graft rejection defined by the treating medical personnel
- Severe infection (necessitating treatment in the inpatient or day-care ward) and severe rejection (excluding BL TCMR)
- All of the three mentioned secondary end-points including COVID-19
- Episodes of infection due to COVID-19
- Estimated glomerular filtration rate (eGFR; current CKD EPI and MDRD abbreviated)
- Rejection detected by protocol biopsy at month 12 post-transplantation: according to BANFF 2019 meeting report (including/excluding BL TCMR) and according to molecular microscope (MMDX)
- *de novo* donor specific antibodies (DSA)

- Plasma TTV load
- TAC trough level and dose
- Unchanged, increased, and decreased TAC trough target levels
- Health related quality of life: SF-36 and MTSOSD-59R questionnaires
- Drug adherence assessed according to paper-based assessment, MEMS® Buttons (AARDEX Group, Switzerland) on TAC blisters, BAASIS questionnaire, claimed prescriptions, psychological evaluation and TAC trough level variability
- Adverse Events and Serious Adverse Events (AEs/SAEs)
- Development of malignoma

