## 7 SAFETY/PHARMACOVIGILANCE

### 7.1 DEFINITIONS

An **Adverse Event (AE)** is any adverse medical occurrence to a subject being administered an IMP and that is not necessarily causally related to that treatment.

- These may be diseases, signs of disease, clinically significant laboratory values or symptoms that occur after the person is included in the trial.
- Also the worsening of a pre-existing disease is to be regarded as AE in this context.

An **adverse reaction (AR)** is any adverse and unintended reaction to an IMP, regardless of its dosage. An adverse reaction is defined as an event that is considered to be at least possibly related to the IMP.

An **Unexpected Adverse Reaction (UAR)** is an adverse reaction that does not match the type or severity of the present reference information (e.g., Investigator's Brochure or SmPC) on the investigational product.

A **Serious Adverse Event (SAE)** or **Serious Adverse Reaction (SAR)** is any adverse event or reaction that:

- results in death, or
- is life-threatening, or
- leads to permanent or serious disability or invalidity, or
- requires inpatient treatment or its prolongation, or
- leads to congenital malformations or birth defects, or
- is medically significant for other reasons (event in which medical intervention became necessary to prevent an outcome considered serious).

A suspected case of an **Unexpected Serious Adverse Reaction** is called **Suspected Unexpected Serious Adverse Reaction (SUSAR)**. A serious adverse reaction is considered unexpected if its type, severity or outcome is not listed in the corresponding reference information. The section 4.8 "Undesirable effects" of the of the respective current valid SmPCs of Advagraf (prolonged release), Prograf (capsules hard) and Prograf (concentrate for solution) serve as reference safety information for purpose of SUSAR reporting.

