**Grade 5**

Death related to AE.

AE Grade 1 to 3 may or may not be serious. These terms are used to describe the intensity of a specific event. However, a severe event may be of relatively minor medical significance (such as severe headache) and is not necessarily serious. For example, nausea lasting several hours may be rated as severe, but may not be clinically serious. Fever of 39°C that is not considered severe may become serious if it prolongs hospital discharge by a day. Seriousness rather than severity serves as a guide for defining regulatory reporting obligations.

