### 7.3 REPORTING OBLIGATIONS

#### 7.3.1 REPORTING OBLIGATIONS OF THE INVESTIGATOR

##### **SAEs**

The investigator shall notify the sponsor (or his designee(s)) immediately (normally **within 24 hours** of notification) of the occurrence of a SAE. The notification shall be made to pharmacovigilance by the investigator or a medical member of the trial group authorized by the investigator.

Electronic reporting via eCRF: After documentation of the SAE in the eCRF, the data is verified by electronic signature and reported to the pharmacovigilance department by means of an automatically generated e-mail. At the same time, the e-mail is sent to the reporting trial site. This e-mail is to be filed in the ISF as evidence of the SAE notification.

If the electronic system is temporarily unavailable, the SAE notification will be submitted on paper (form in ISF) via fax or e-mail to the Pharmacovigilance Department. As soon as the system is available again, the documentation in the eCRF must be made up for.

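### Section 7.2 makes an adverse event an SAE for becoming a persistent secondary disease, a route to seriousness that the SAE definition in 7.1 does not contain, with timing that conflicts with 7.3.1

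*Protocol*

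**What the plan says.** Protocol section 7.1 defines an SAE by six alternatives: death, threat to life, disability, inpatient treatment or its prolongation, congenital malformation or birth defect, and other medical significance. The two closest to a lasting condition are the disability criterion, "leads to permanent or serious disability or invalidity, or" (the list then goes on), and the last one, "is medically significant for other reasons (event in which medical intervention became necessary to prevent an outcome considered serious".

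Section 7.2, on documentation, adds: "If the adverse event develops into a persistent secondary disease, it should be classified as an SAE and documented accordingly". The sentence sets this for the close of the trial. The protocol does not define the key term. The same section already has a field for how an event ended: "outcome of the event (recovered, recovering, not recovered, recovered with sequelae, fatal, unknown".

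Three other places give the label its weight:
- Section 3.3 lists "Adverse Events and Serious Adverse Events (AEs/SAEs" among the secondary endpoints.
- Section 7.2.1 states: "Seriousness rather than severity serves as a guide for defining regulatory reporting obligations".
- Section 7.3.1 sets the timing for SAEs: "The investigator shall notify the sponsor (or his designee(s)) immediately", normally within 24 hours.

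**The concern.** An SAE table is interpretable only if every site applies one definition of seriousness. Here sites have two. Under 7.1, duration does not make an event serious. Under 7.2, persistence as a secondary disease does.

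Conditions that could fall between the two rules are foreseeable. Section 6.16.1 names new-onset diabetes, raised lipids and arterial hypertension among its safety parameters. Section 5.2 lists diabetes, hypertension, hyperlipidaemia and tremor as tacrolimus effects. Each can last without admission or disability.

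Section 10.1 frames the main goal as non-inferiority with respect to safety, so readers will look at the SAE comparison even though it is secondary. Section 5.11.1 says that the investigator is not blinded to allocation. An undefined and discretionary route to SAE status is therefore applied by people who know the arm. Thirteen centres may also resolve the conflict differently.

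**Working it through.** **Step 1. The two rules side by side.**

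| | Section 7.1 | Section 7.2 sentence |
|---|---|---|
| Trigger | One of six outcomes or interventions | Becoming a persistent secondary disease |
| Does persistence alone suffice? | No | Yes, read literally |
| Must a 7.1 criterion be met? | Yes | Not stated |
| Key term defined? | Criteria are listed | No |

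Take a new, lasting rise in lipids managed as an outpatient. It involves no death, threat to life, disability, admission or birth defect, and would not normally need an intervention to prevent a serious outcome. It is non-serious under 7.1 and can be an SAE under 7.2.

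**Step 2. Timing.** Section 7.3.1 requires immediate notification of an SAE. Section 7.2 places the documentation at the end of the trial, which section 3.7 defines as the last visit of the last patient. Section 7.4 schedules DSMB safety analyses after 65 and 130 included patients, that is at 65/260 = 25% and 130/260 = 50% of planned inclusion. It says that SAEs are analysed according to the randomisation sequence, which I take to mean by arm. An event labelled only through 7.2 can therefore be non-serious at both scheduled reviews and serious in the final table.

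**Step 3. What is not touched.** The composite in section 3.2 does not include SAEs. The power in section 10.2 reproduces without them: Φ(0.20/√(0.3·0.7/120 + 0.4·0.6/120) − 1.96) = 0.9042, against the stated 90.42%.

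**Step 4. Direction of the distortion.** The protocol states no SAE rate and no rate of persistent non-serious events, so this is an illustration on assumed values only. Let s be the proportion with an SAE under 7.1, and q the proportion with a persistent event that 7.1 would not count, independent of s. The proportion labelled with an SAE is then 1 − (1 − s)(1 − q). S is the standard arm and T the TTV-guided arm.

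| s in S, T | q in S, T | Labelled in S | Labelled in T | T − S (points) |
|---|---|---|---|---|
| 40%, 30% | 0, 0 | 40% | 30% | −10 |
| 40%, 30% | 10%, 10% | 1 − 0.6·0.9 = 46% | 1 − 0.7·0.9 = 37% | −9 |
| 40%, 30% | 20%, 20% | 1 − 0.6·0.8 = 52% | 1 − 0.7·0.8 = 44% | −8 |
| 40%, 30% | 30%, 30% | 1 − 0.6·0.7 = 58% | 1 − 0.7·0.7 = 51% | −7 |
| 40%, 30% | 20%, 10% | 52% | 37% | −15 |
| 40%, 30% | 10%, 20% | 46% | 44% | −2 |
| 40%, 40% | 10%, 20% | 46% | 1 − 0.6·0.8 = 52% | +6 |

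The labelled proportion rises in every row where q is above zero. The difference shrinks when q is equal in the arms. When q is unequal it can widen, shrink further, or appear where there was none.

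**The case against.** The best defence is that the sentence is narrower than it looks. It speaks of an event that develops into a persistent secondary disease, not of every event unresolved at the final visit. It could be meant as guidance on applying the disability or medical-significance criteria to lasting sequelae, and some such conditions would meet 7.1 anyway. That reading is possible, but the text neither states it nor defines the term, so the conflict stands.

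A second defence is that grade, outcome, action taken and dates are recorded for every event, so sensitivity tables could be built, and their layout belongs in the SAP. This is partly right. But the list in 7.2 asks only for serious or non-serious, not for the criterion met. Unless the eCRF records the criterion, events made serious only by 7.2 can be separated only indirectly.

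A third defence is that the DSMB example on SAEs carries its own qualifier (CTCAE above grade 3, or severe or medically significant) and that section 7.4 sets no statistical stopping rule. Mild chronic conditions would not clearly count there. This stands for that example. The general SAE review by the DSMB has no such qualifier.

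A reader might also infer more than the protocol supports:
- **That arm differences are diluted towards zero.** This needs equal added rates. Tacrolimus targeting is what the arms vary, several candidate conditions are listed tacrolimus effects, and the classifier is unblinded, so equality cannot be presumed.
- **That the inflation has a known size.** Any count of relabelled patients would rest on assumed rates.
- **That most safety parameters are chronic and mild.** Section 6.16.1 has 15 entries. Diabetes, lipids and hypertension are three of them, while others, such as death, graft loss, cardiovascular events and malignoma, are of a different kind.

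**Conclusion.** Wrong as written, minor severity. Section 7.2 gives a route to SAE status that the definition in 7.1 lacks, rests it on an undefined term, and sets a timing that conflicts with 7.3.1. If sites follow it literally, SAE counts can be inflated and the comparison of arms on this secondary endpoint distorted in either direction. No size can be given, because the protocol supplies neither an SAE rate nor a rate of persistent non-serious events. The figures above show direction only, and the 40% and 30% used there match the primary-endpoint assumption, which is not an SAE rate. The conclusion rests on the literal reading of one sentence and on the absence of a definition elsewhere in the protocol.

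**What to change.** Reconcile 7.2 with 7.1:
1. Delete the sentence, or restrict it so that SAE status depends only on the 7.1 criteria.
2. Report persistent adverse events by arm from the existing outcome field, using the categories for not recovered and recovered with sequelae.
3. State that an event that later comes to meet a 7.1 criterion is reported on the 7.3.1 timeline from that point, not held to the end of the trial.

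The cost is a one-sentence change in the protocol and matching eCRF guidance. No new data are needed. If events have already been labelled through 7.2, they should be checked against the 7.1 criteria before the SAE table is produced.

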### 7.2.1 SEVERITY OF ADVERSE EVENTS

The severity of clinical AEs is graded from 1 to 5 in accordance to the Common Terminology Criteria for Adverse Events (CTCAE; Version 5.0, 27.11.2017; NCI) and reported on specific AE pages of the eCRF. If the severity of an AE worsens during study drug administration, only the worst intensity should be reported on the AE page. If the AE lessens in intensity, no change in the severity is required. If an AE occurs during a washout or placebo run-in phase and afterwards worsens during the treatment phase, a new AE page must be filled in with the intensity observed during study drug administration.

#### **Grade 1**

Mild; asymptomatic or mild symptoms; clinical or diagnostic observations only; intervention not indicated.

#### **Grade 2**

Moderate; minimal, local or noninvasive intervention indicated; limiting age-appropriate instrumental activities of daily living (ADL).

#### **Grade 3**

Severe or medically significant but not immediately life-threatening; hospitalization or prolongation of hospitalization indicated; disabling; limiting self-care ADL.

#### **Grade 4**

Life-threatening consequences; urgent intervention indicated.

**Grade 5**

Death related to AE.

AE Grade 1 to 3 may or may not be serious. These terms are used to describe the intensity of a specific event. However, a severe event may be of relatively minor medical significance (such as severe headache) and is not necessarily serious. For example, nausea lasting several hours may be rated as severe, but may not be clinically serious. Fever of 39°C that is not considered severe may become serious if it prolongs hospital discharge by a day. Seriousness rather than severity serves as a guide for defining regulatory reporting obligations.

**7.2.2 RELATIONSHIP TO STUDY DRUG**

For all AEs, the Investigator will assess the causal relationship between the study drug and the AE using his/her clinical expertise and judgment according to the following algorithm that best fits the circumstances of the AE:

**Not related**

- May or may not follow a temporal sequence from administration of the study product
- Is biologically implausible and does not follow known response pattern to the suspect study drug (if response pattern is previously known).
- Can be explained by the known characteristics of the subject's clinical state or other modes of therapy administered to the subject.

**Unlikely**

- There is a reasonable temporal relation between the AE and the intake of the study medication, but there is a plausible other explanation for the occurrence of the AE.

**Possibly**

- The AE has a reasonable temporal relationship with drug administration.
- The AE may equally be explained by the study subject's clinically state, environmental or toxic factors, or concomitant therapy administered to the study subject.
- The relationship between study drug and AE may also be pharmacologically or clinically plausible.

**Probably**

- There is a reasonable temporal relation between the AE and the intake of the study medication, and plausible reasons point to a causal relation with the study medication.

**Related**

- Reasonable temporal relation between the AE and the intake of the study medication and
- There is no other explanation for the AE and
- Subsidence or disappearance of the AE on withdrawal of the study medication and
- Recurrence of the symptoms on restart at previous dose (only applies for re-institution of medication).

**Not assessable**

- The causal relationship between the study drug and the AE cannot be judged.

**7.2.3 SPECIAL FEATURES WITH SAES**

The following points must be observed when documenting SAEs:

- the corresponding AE must be marked as **serious** in the eCRF.
- each SAE must be documented as completely as possible (in the event of death, an autopsy should be performed if possible and the report made available to the sponsor).

#### 7.2.4 DEATHS

Deaths that are not due to AE must also be documented in the eCRF.

Safety parameters will be assessed at every study visit. To detect TAC-related AEs and toxicity lab work will be performed according to routine clinical care at every study visit. In addition vital signs, neuropsychiatric, sensoria, cardiovascular, bronchial, gastrointestinal, dermatologic, musculoskeletal and urogenital alterations will be assessed at every study visit. In addition to the age-adapted tumour screening recommended for the general population, annual skin examinations will be recommended to participants. check-ups on patients concerning AEs and infections will be performed via telephone according to preferred contact numbers and times every two weeks. Multiple calls will be performed: a minimum of 3 at two different days at varied times. Safety parameters will be recorded in the eCRF.

### 7.3 REPORTING OBLIGATIONS

#### 7.3.1 REPORTING OBLIGATIONS OF THE INVESTIGATOR

##### **SAEs**

The investigator shall notify the sponsor (or his designee(s)) immediately (normally **within 24 hours** of notification) of the occurrence of a SAE. The notification shall be made to pharmacovigilance by the investigator or a medical member of the trial group authorized by the investigator.

Electronic reporting via eCRF: After documentation of the SAE in the eCRF, the data is verified by electronic signature and reported to the pharmacovigilance department by means of an automatically generated e-mail. At the same time, the e-mail is sent to the reporting trial site. This e-mail is to be filed in the ISF as evidence of the SAE notification.

If the electronic system is temporarily unavailable, the SAE notification will be submitted on paper (form in ISF) via fax or e-mail to the Pharmacovigilance Department. As soon as the system is available again, the documentation in the eCRF must be made up for.

##### **Follow Up**

If further information on the SAE becomes available at a later date, it must also be reported immediately to the sponsor (or his representative). The trial site's report is checked for completeness and plausibility and, if necessary, further inquiries are made and followed up.

##### **Death of a subject**

In the event of the death of a subject, the trial site shall provide the competent ethics committee, the higher federal authority and the sponsor (or its authorised representative) with any additional information required for the performance of their duties (upon request).

#### 7.3.2 REPORTING OBLIGATIONS OF THE SPONSOR

##### **AEs**

The Sponsor must document in detail all adverse events reported to him and, upon request, submit these to the Member States concerned.

### SUSARs

The sponsor must inform the Member States concerned and the investigators involved in the clinical trial about every suspected case of an unexpected serious adverse drug reaction (SUSAR) that comes to his attention immediately, but at the latest **within 15 days** of its discovery.

For every suspected case of a suspected unexpected serious adverse reaction (SUSAR) reported to the sponsor, that has led to **death** or is **life-threatening**, the sponsor must immediately, but at the latest **within seven days** after becoming aware of it, provide the Member States concerned and the investigators involved in the clinical trial with all information relevant to the evaluation and within a maximum of **eight further days** with the other relevant information.

### Re-evaluation of the benefit-risk assessment

The Sponsor shall immediately, but **at the latest within 15 days** of its notification, inform the Member States concerned of any factual situation that requires a re-examination of the benefit-risk assessment of the IMP. This includes in particular:

- subject case reports of expected serious adverse reactions (SARs) with an unexpected outcome,
- increase of the frequency of expected serious adverse reactions (SARs) that are considered clinically relevant,
- suspected cases of serious unexpected adverse reactions (SUSAR) that occurred after the subject had already terminated the clinical trial,
- events related to the conduct of the trial or the development of the IMP that may potentially affect the safety of the subjects.

